### Outcome measures

This study distinguishes between two different, but correlated, types of outcomes.

#### Effectiveness outcomes

##### Primary outcome measures

*Initiation*: Patients who receive a new prescription will be considered initiators if they obtain their prescriptions in a community pharmacy during the following month [6]. Sensitivity analysis will be performed for a follow-up period of 3 months. Prescription and dispensation databases from SIDIAP will be compared to classify prescriptions as initiated and non-initiated.

##### Secondary outcome measures

*Secondary adherence*: Implementation during the follow-up period will be calculated 
based on the proportion of days covered (PDC). PDC is the number of days in which 
17
the prescribed medication is available divided by the number of days of the period 
when the prescription is active within the study period (365 days). This value ranges 
from 0 to 1 and is multiplied by 100 to obtain a percentage of adherence [75]. PDC has 
been proved to represent patient behaviour and treatment continuity [76, 77] accurately.
Persistence will be defined as the time from initiation until discontinuation of the 
prescribed treatment, accepting a gap no longer than two months. Patients will be 
classified as adherent or otherwise by combining these two variables; that is, patients 
with PDC>80% during the follow-up year, with medication gaps up to 2 months, will be 
considered adherent.*Reduction of CVR*: The Framingham Risk Score will be calculated using clinical outcomes, like diabetes diagnosis, total cholesterol, high-density lipoprotein cholesterol, systolic and diastolic blood pressure, and sociodemographic variables including age and sex, and tobacco use [78] one year after the index prescription.

##### Other outcome measures

These data will be collected from the SIDIAP database for the 12 months after the index prescription.*Clinical parameters:* Clinical parameters assessed will depend on the diagnosis. Patients with type II diabetes: glycated haemoglobin, glomerular filtration rate, impaired fasting glucose; with dyslipidaemia: high-density lipoprotein, low-density lipoprotein and total cholesterol; and with hypertension: systolic and diastolic blood pressure.*Cardiovascular events:* Events related to CVD and diabetes, categorised according to the International Classification of Diseases, 10th version (ICD10). Table 2 shows the list of events considered.

#### Cost-effectiveness outcomes

All cost data will be collected from the SIDIAP database and will be understood to cover the use of healthcare and social resources and sick leave for each patient, 12 months before and after the index prescription.

The following direct costs will be considered: visits to PC (GP and nurse; on-site and home visits) and emergency room (PC or secondary care); referral to secondary care; hospital admissions (inpatient admissions and outpatient consultations); use of social care services (such as visits to the social worker); and outpatient diagnostic tests and medication use. Indirect costs considered include productivity losses (as sick leave).

#### Sociodemographic variables and diagnostics

Sociodemographic characteristics of the patients (sex, age, nationality, socioeconomic status, tobacco use and diagnoses at baseline), the prescribing GP (sex, age, nationality, years of work experience, specialisation and tutoring of medical residents) and the characteristics of the PC team (teaching centre, rurality, socioeconomic status of the reference area, number of GPs) will be gathered from the SIDIAP database. Additional information on all healthcare professionals (PC centre or pharmacy where they work, sex, occupation and years of work experience) will be also gathered through questionnaires [53].

### Sample size

According to previous results, the proportion of non-initiation of medications for CVD and diabetes in Catalonia is between 8–13% [18]. For sample size calculations, a proportion of 10% has been assumed. The sample size was estimated based on calculations for cluster randomised controlled trials [79]. Assuming a reduction in the incidence of non-initiation of 3%, a power of 80% and a significance level of 5%, given that the intracluster correlation coefficient for PC teams is 0.01, and assuming that, on average, each GP issues 30 new prescriptions of the selected medicines in 6 months, accounting for 10% of losses (due to incompleteness of data in clinical records), the necessary sample is 3,878 prescriptions and 130 GPs.

Considering 80% of urban PC centres in Catalonia and assuming a minimum number of five GPs per urban PC team and 2 per rural PC team, we will contact twenty-four PC teams to invite them to participate; fourteen from urban areas and ten from rural areas. PC teams will be included until the sample size is reached, i.e., 65 GPs are included in both the control and intervention groups.

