### The Initial Medication Adherence (IMA) study

The IMA study has an effectiveness-implementation hybrid design [48]; it consists of a pragmatic cluster randomised controlled trial (cRCT) along with a process evaluation to understand the effect of the IMA intervention in terms of effectiveness and cost-effectiveness, and to redefine the intervention before its implementation. Hybrid designs aim to evaluate the effectiveness of interventions while gathering information for their implementation in clinical care [49, 50] and are expected to speed the translation of research findings into routine practice [49, 50].

The IMA intervention was developed within the Medical Research Council (MRC) Framework for Complex Interventions [51, 52]. Further details on the design of the intervention and process evaluation are described elsewhere [53].

Following the MRC guidelines, several studies were carried out to identify the evidence base and develop the theory on which the IMA intervention is based. Using real-world data (RWD), the prevalence of non-initiation was estimated to be 17% in Catalan PC; for CVD and diabetes treatments specifically, it ranged between 5.7% (ACE inhibitors) and 9.1% (antiplatelet). Factors explaining non-initiation were also identified [9, 18, 30]. Additionally, to understand patients’ motivations for non-initiation, two qualitative studies based on Grounded Theory were conducted [34, 35]. The results of these studies were used to generate the Theoretical Model of Medication Non-Initiation [34, 35]. Finally, the evidence on interventions aiming to improve initiation was reviewed.

An initial version of the IMA intervention was drafted taking into account all the available evidence; it was based on the Theoretical Model of Medication Non-Initiation [34, 35]. It is a multidisciplinary intervention that promotes health literacy and shared-decision making (SDM) to improve medication initiation and secondary adherence and reduce cardiovascular risk (CVR).

To increase the acceptability and transferability of the intervention, discussion groups were then conducted with GPs, nurses, community pharmacists and other healthcare professionals, who made suggestions for optimisation, defined the limitations of the intervention and anticipated barriers to its implementation.

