**Fig. 1 Fig1:**
[figure not shown]
Summary of the IMA-cRCT Research Project and timeline

The intervention assignment is cluster-based considering PC teams and two parallel arms: usual care in the control group and the IMA intervention in the intervention group. Twenty-four PC teams will participate in the trial.

The Standard Protocol Items: Recommendations for Interventional Trials (SPIRIT) checklist for study protocols [55, 56] is provided in Additional file 1. Details about the pragmatic design of the IMA-cRCT are provided in the Pragmatic Explanatory Consortium Indicator Summary (PRECIS-2) [57] wheel scheme in Additional file 2.

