### Randomisation

Paired PC teams included in the study will be randomised (1:1) into two parallel groups using a computerised random number generator. Concealment of allocation was guaranteed at the PC team level: PC teams will not be randomised until both teams in each pair agree to participate in the study. However, at the patient level, it is not possible to guarantee concealment of allocation due to the intrinsic characteristics of the study design by clusters.

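### The sample size applies a PC-team ICC to the cluster size of a single GP; with 24 randomised teams and that ICC, power for 10% v 7% is about 49–55%, not 80%

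*Protocol article*

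**What the plan says.** The Sample size section of the protocol article sets the control rate: "For sample size calculations, a proportion of 10% has been assumed". It assumes a 3% reduction, 80% power, 5% significance and 10% losses. The clustering inputs are "given that the intracluster correlation coefficient for PC teams is 0.01, and assuming that, on average, each GP issues 30 new prescriptions", and the result is that "the necessary sample is 3,878 prescriptions and 130 GPs".

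The unit of assignment is the PC team. The Randomisation section says "Paired PC teams included in the study will be randomised (1:1) into two parallel groups", and the Design section says "Twenty-four PC teams will participate in the trial". The Sample size section plans 14 urban and 10 rural teams, with minima of five and two GPs per team, and lets inclusion continue until each arm has 65 GPs. The Statistical analysis section clusters all analyses on both PC team and GP.

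**The concern.** A design effect multiplies an ICC by the size of the cluster to which that ICC belongs. Here the ICC belongs to the PC team and the cluster size to a single GP. The average team contains more than five GPs (130/24 = 5.4), so a team-level correlation acts on a cluster more than five times larger than the one entered. The variance of the treatment comparison is understated and the power overstated.

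The primary outcome, initiation, is affected. Anyone who later read a non-significant result against the stated 80% would give it more weight than the design can bear.

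**Working it through.** **Inputs.** From Sample size: control rate p1 = 0.10; reduction 3 points, so p2 = 0.07; power 80%; α = 5%; ICC 0.01 for PC teams; 30 prescriptions per GP; 10% losses. From Design and Randomisation: 24 teams, 1:1. The text does not say whether the test is two-sided or the reduction absolute; both readings are taken because they reproduce the stated figure.

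**1. Reproduce the plan's figure.**

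- n per arm = (1.960 + 0.842)² × (0.10 × 0.90 + 0.07 × 0.93) / 0.03² = 1,352.6; both arms 2,705.2.
- Design effect = 1 + (30 − 1) × 0.01 = 1.29; 2,705.2 × 1.29 = 3,489.8.
- Losses: 3,489.8 / 0.9 = 3,877.5, i.e. 3,878.
- GPs: 3,878 / 30 = 129.3, i.e. 130.

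Both stated figures come out. No design effect (about 3,013, pooled variance), a one-sided test (3,062) or a continuity correction with m = 30 (4,076) does not give 3,878.

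**2. Same inputs, with the randomised team as the cluster.** Design effect = 1 + (m − 1) × 0.01, with m = N/24. SE = √[0.1551 × design effect / (N/2)], where 0.1551 = 0.09 + 0.0651. Power = Φ(0.03/SE − 1.96).

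| | After 10% losses | No losses |
|---|---|---|
| N | 3,490 | 3,878 |
| m | 145.4 | 161.6 |
| Design effect | 2.44 | 2.61 |
| SE | 0.01474 | 0.01444 |
| Power, normal | 53% | 55% |
| Power, t on 22 df | 49% | 51% |
| Detectable difference at 80% power, normal | 4.0 points | 3.9 points |
| Same, t on 22 df | 4.2 points | 4.1 points |

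Unequal teams: GP numbers of 5 in 14 teams and 2 in 10 teams have a coefficient of variation of 0.39. Using 1 + [(1 + 0.39²)m − 1] × 0.01, normal power falls to 49% (N = 3,490) or 51% (N = 3,878).

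**3. Can more prescriptions repair it?** As m grows without limit in 24 teams, the SE tends to √(0.1551 × 0.01 / 12) = 0.01137. Power then tends to Φ(0.03/0.01137 − 1.96) = 75%. At a team ICC of 0.01, 24 teams cannot reach 80% for this effect.

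**4. Number of teams.** The minima give 14 × 5 + 10 × 2 = 90 GPs, or 3.75 per team. Reaching 130 GPs at that average takes 130/3.75 = 34.7, about 35 teams.

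- N = 3,490, m about 101: power 61% with equal teams, 58% with unequal teams.
- N = 3,878, m about 112: power about 63–64% with equal teams.

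**5. Dependence on the ICC** (24 equal teams, N = 3,490, normal).

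| Team ICC | Design effect | Power |
|---|---|---|
| 0.002 | 1.29 | 80% |
| 0.005 | 1.72 | 68% |
| 0.01 | 2.44 | 53% |
| 0.02 | 3.89 | 36% |

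The design effect of 1.29 is recovered when the team ICC is 0.29/144.4 = 0.002.

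**The case against.** **The number of teams is not fixed.** Inclusion runs until 65 GPs per arm are in, and 24 teams at the minima supply only 90 GPs. This stands, so a reader who takes about 50% as the power in all circumstances goes further than the document allows. The Design section does state 24 teams, which makes that a fair base case, and about 35 teams still leave power at 58–64%.

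**The ICC of 0.01 may be a GP-level value.** If so, team-level power cannot be computed from this document. The text, however, attaches 0.01 to PC teams, and the team ICC would then have to be stated.

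**Pairing and covariate adjustment may recover precision.** Pairs are formed on location and stratified on predictors of non-initiation, and the models adjust for predictors. Some gain is plausible, but the calculation claims none. The residual team ICC would have to fall to about 0.002, or 0.0027 with no losses.

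**Losses may not touch this outcome.** The Strengths and limitations section says that missing clinical information will not affect initiation. That favours the no-loss column, which is only about 2 percentage points better.

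**The control rate.** A reader might infer that 10% is too high and power lower still, because the Background says of non-initiation for these drugs that "it ranged between 5.7% (ACE inhibitors) and 9.1% (antiplatelet". The documents do not support this. The Sample size section cites 8–13% for the same drug classes in Catalonia, and 10% lies inside it. With the reduction held at 3 points, a lower control rate raises power (24 teams, N = 3,490, normal): 57% at 9.1%, 63% at 8%, 81% at 5.7%. Power falls only if the effect is recast as a fixed relative reduction, which the plan does not state.

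**The test itself.** A reader might also infer an inflated type I error. The planned models cluster on PC team and GP, so the fault lies in the power claim. Nor does the document say that a null result will be taken as proof of no effect; that is a risk for readers.

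**Conclusion.** The calculation is wrong as written. The arithmetic is sound, but the ICC and the cluster size refer to different levels. On the plan's own inputs (24 teams, team ICC 0.01, 10% v 7%), the design effect is about 2.4–2.6 instead of 1.29. Power is about 49–55%, slightly lower with unequal teams, and the detectable difference at 80% power is about 4 points. With about 35 teams, power is about 58–64%.

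These figures depend on 0.01 holding at team level and on no credit for pairing. The stated 80% would hold only at a team ICC of about 0.002 or lower. The finding does not depend on the choice of control rate, and 10% is not faulted here.

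**What to change.** In the Sample size section:

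- Recompute the design effect with the PC team as the cluster.
- Restate power and detectable difference for the planned number of teams, over a range of team ICCs such as 0.002 to 0.02, allowing for unequal team sizes.
- Reconcile the 24 teams with the rule of 65 GPs per arm, so that the power refers to a definite number of teams.
- If 0.01 is a GP-level ICC, say so and state the PC-team ICC used.
- If credit is taken for pairing or adjustment, give the assumed gain.

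State also that a non-significant primary result will be interpreted by its confidence interval and not against the 80% figure.

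The cost is one rewritten paragraph and a less favourable stated power. No extra recruitment is required. For scale only, 80% power at about 145 analysed prescriptions per team and ICC 0.01 would take about 46 teams.

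### At the assumed minimum of 5 GPs per urban and 2 per rural team, the planned 24 teams supply 90 GPs, not the 130 required, and no higher yield is stated

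*Protocol article*

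**What the plan says.** The Sample size section works out a requirement of 3,878 prescriptions and 130 GPs. It converts this into teams as follows: "assuming a minimum number of five GPs per urban PC team and 2 per rural PC team, we will contact twenty-four PC teams", namely "fourteen from urban areas and ten from rural areas". The next sentence gives a recruitment rule: "PC teams will be included until the sample size is reached, i.e., 65 GPs are included in both the control and intervention groups".

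The Inclusion criteria for PC teams use the same two minima as the entry threshold for a team. The Design section states the trial size without qualification: "Twenty-four PC teams will participate in the trial". The Methods part of the Abstract also gives 24 teams. The article nowhere states an expected number of GPs per team above the minima.

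**The concern.** The number of teams is presented as following from an assumed number of GPs per team, and it does not follow. Multiplying out the printed figures gives 90 GPs, 40 fewer than the requirement in the paragraph before.

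The article then leaves two rules for the end of recruitment. One is 24 teams; the other is 65 GPs in each group. They agree only if teams bring clearly more GPs than the assumed minima. Otherwise a reader cannot tell which rule governs. What is at stake is whether the stated 80% power for initiation, the primary outcome, is tied to the number of teams the trial announces.

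**Working it through.** **Inputs, all from the Sample size section unless noted.** Control non-initiation 10% ("For sample size calculations, a proportion of 10% has been assumed"); reduction of 3, read as percentage points (10% to 7%); power 80%; significance level 5%, read as two-sided; intracluster correlation 0.01; 30 prescriptions per GP; 10% losses; 14 urban and 10 rural teams; minima of 5 and 2 GPs. Allocation 1:1 is from Randomisation. The percentage-point and two-sided readings are the ones that reproduce the plan's figure.

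**Step 1: reproduce the requirement.**
- Per arm, unpooled variance: n = (1.96 + 0.8416)² × (0.10 × 0.90 + 0.07 × 0.93) / 0.03² = 1,352.6.
- Design effect: 1 + (30 − 1) × 0.01 = 1.29.
- Total with losses: 2 × 1,352.6 × 1.29 / 0.9 = 3,877.5, so 3,878 prescriptions.
- GPs: 3,878 / 30 = 129.3, so 130 at 65 per group.

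The requirement reproduces exactly. The problem lies only in the step from GPs to teams.

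**Step 2: what 24 teams supply at the minima.**
- GPs: 14 × 5 + 10 × 2 = 90, which is 40 short (31% below 130).
- Prescriptions: 90 × 30 = 2,700, which is 1,178 short (30% below 3,878).
- The urban–rural split is not the cause. An 80% urban share would give 24 × (0.8 × 5 + 0.2 × 2) = 105.6 GPs, and even 24 urban teams would give 24 × 5 = 120.

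**Step 3: power if every team enrols only its minimum.**
- Analysed prescriptions: 2,700 × 0.9 = 2,430, or 1,215 per arm.
- Power = Φ(0.03 / √(0.1551 × 1.29 / 1,215) − 1.96) = Φ(0.38), about 65%.
- Crediting a full seventh month (35 prescriptions per GP) gives 90 × 35 = 3,150 prescriptions, 81% of the requirement, and about 71% power. The Intervention section says that the extra month allows for holidays, so this is generous.

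**Step 4: what would make the figures agree.**
- With 24 teams: 130 / 24 = 5.4 GPs per team on average. If rural teams give 2, urban teams must give (130 − 20) / 14 = 7.9.
- At the minima and the same mix: 90 / 24 = 3.75 GPs per team, and 130 / 3.75 = 34.7, so about 35 teams.

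**The case against.** The strongest reply is that 5 and 2 are floors. Inclusion criteria and Sample size both call them minima, and an average of 5.4 GPs per team is compatible with them. The article does not claim that 24 teams at the minima give 130 GPs, and its requirement is computed correctly. This stands. The gap is an unsupported planning figure, not a miscalculated sample size.

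A second reply is that the rule of 65 GPs per group protects the size. This also stands as far as it goes: that rule continues until the size is reached, and 287 teams are assessed for eligibility. But it protects the size only if the number of teams may exceed 24, and Abstract and Design give 24 as the trial's size with no such allowance.

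Three stronger readings are tempting and are not supported.
- A reader might infer that the trial will be a third too small. That needs every team at its floor and the 65-GP rule set aside.
- A reader might infer that the plan counts every contacted team as a participant and ignores refusals. Recruitment and selection provides an ordered replacement list for each pair, and Randomisation waits until both teams of a pair agree.
- A reader might infer that the target could be chased by adding GPs inside the same teams. The rule speaks of including teams, and the article sets out no such route.

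**Conclusion.** The point holds as a mismatch between figures that the trial relies on. The 24 teams do not follow from the stated assumption on GPs per team: that assumption yields 90 GPs and 2,700 prescriptions against 130 and 3,878. At the minima, 24 teams and 65 GPs per group cannot both be met.

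The arithmetic gap and the conflict between the two rules need no assumption beyond the printed figures. The 65% power is conditional: it assumes that all teams enrol at their minima, that no teams are added, 10% losses, and the plan's own design effect of 1.29. Whether that design effect uses the right cluster size, given that "the intracluster correlation coefficient for PC teams is 0.01", is a separate question and is not used here. The documents do not show that the trial must be underpowered. Severity: moderate.

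**What to change.** Make the Sample size paragraph agree with itself and with Abstract and Design, in one of these ways:

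1. If 24 teams is the plan, state the average that they must supply, 5.4 GPs per team (7.9 per urban team if rural teams give 2), as the planning assumption, and keep 5 and 2 as entry thresholds only.
2. If 65 GPs per group is the rule, say that 24 is provisional and that team pairs are added from the eligible list until 65 GPs per group are reached. Give the upper end: about 35 teams at the minima. Change the unqualified 24 in Abstract and Design accordingly.
3. If 24 is a hard limit, report what it guarantees at the minima (90 GPs, 2,700 prescriptions, about 65% power on the plan's own design effect) beside the 80% target.

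The textual cost is one paragraph and two matching sentences. The first option leaves the stated size and power unchanged. The second leaves them unchanged but may mean recruiting and training more teams. Only the third makes the stated power less favourable.

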### Statistical analysis

All analyses will be conducted following the intention to treat principle, including all patients treated by the GPs who fulfil inclusion criteria.

Poor registration of clinical outcomes and CVR data in electronic medical records may generate missing values. To deal with missing data, we will first explore the pattern of the missing data by using logistic regression models to test whether the observed variables predict the presence of missing data. If the existence of missing data is indeed explained by observed variables, a Missing at Random pattern will be assumed and multiple imputations with chained equations will be used to impute missing data. If possible, the imputation models will use any covariate that is predictive of missingness as well as all the variables that will be later used in the effectiveness and cost-effectiveness models [80]. The number of imputations will be determined by the fraction of missing information [81, 82]. The subsequent analyses will be conducted in each of the imputed datasets and the estimators will be pooled using Rubin’s rules [81].

A descriptive analysis, based on sociodemographic variables and health problems, will be performed to compare groups at baseline. Characteristics of participating healthcare professionals will also be compared between groups. Continuous variables will be presented with means and standard deviation; categorical variables will be presented with frequency and percentages. Differences between groups in these variables will be estimated using multilevel linear regression for continuous variables and multilevel logistic regression for categorical variables, considering the group as the independent variable in both cases.

The impact of the intervention will be assessed overall and for each pharmacotherapeutic subgroup, i.e., the 3rd level of the Anatomical Therapeutic Chemical (ATC) Classification System [83].

All models will be controlled for patient sociodemographic and clinical characteristics that have been described in the literature as predictors of non-initiation [9, 18] and which show statistically significant differences between intervention and control group at baseline; and will be performed using multilevel techniques. The basic unit of analysis will be either prescription or patient, based on the analysis. All analyses will be clustered at the level of PC team and GP.

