#### Effectiveness

To assess the impact of the IMA intervention on initiation, a multilevel logistic regression will be estimated in which the dependent variable will be initiation and the independent variable will be the group.

A multilevel logistic regression model will be performed to compare the proportion of adherent patients between the intervention and control groups. In the model, the dependent variable will be adherence and the independent variable will be the group.

Multilevel repeated measure models will be used in which clinical parameters and CVR (the dependent variables) are considered several times, at diverse time points during the follow-up period.

The interaction ‘group x time’ will be used to evaluate the impact of the intervention (independent variables).

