##### Sensitivity analysis

Per-protocol analyses will be performed including only patients who received a prescription by those GPs who attended both training sessions. Additionally, two complete case analyses will be performed: one considering only those patients attended by GPs who completed the 7-month study period, and another using only non-imputed data.

To assess uncertainty in the output of the models, a sensitivity analysis will be performed without controlling the models for baseline covariates to assess their effect on the results of the cRCT [84].

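### Known predictors of non-initiation enter the models only if they differ significantly between arms at baseline, so the trial data choose the primary model and power is given up

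*Protocol article*

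**What the plan says.** The Statistical analysis section of the protocol sets one covariate rule for everything: "All models will be controlled for patient sociodemographic and clinical characteristics" that meet two conditions. They must be characteristics "that have been described in the literature as predictors of non-initiation" (references 9 and 18), and ones "which show statistically significant differences between intervention and control group at baseline". On the natural reading both conditions must hold. The baseline comparison that supplies the second condition is described in the same section: "Differences between groups in these variables will be estimated using multilevel linear regression for continuous variables and multilevel logistic regression for categorical variables", with group as the explanatory variable. No significance level is given for it.

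The primary model, under Effectiveness, adds no covariate list of its own: "a multilevel logistic regression will be estimated in which the dependent variable will be initiation and the independent variable will be the group". The only check on covariates, under Sensitivity analysis, removes them all: models are run "without controlling the models for baseline covariates to assess their effect on the results of the cRCT".

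Two covariates escape the rule. Under Cost-effectiveness analysis, cost models are adjusted for costs in the preceding 12 months and the cardiovascular risk (CVR) model for baseline CVR, with no test first.

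**The concern.** A baseline significance test is a poor way to choose covariates. What makes a covariate worth including is its relation to the outcome. The test measures only how far the arms differ on it, and under randomisation that is a matter of chance. The rule thus takes a list of variables already known to predict the outcome and discards nearly all of them.

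Three things are at stake. The primary model is settled only after the arms have been compared, so its content cannot be stated in advance. The precision offered by known predictors is mostly lost. And an imbalance that matters but falls short of significance is left alone, in a trial with 24 randomised teams where such a test has little power. Because adjusted and unadjusted odds ratios differ even without confounding, the quantity that the primary model estimates also depends on which p-values cross the threshold.

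**Working it through.** **Inputs from the protocol.** Sample size section: 10% non-initiation, reduction of 3% (read as 10% to 7%), power 80%, significance level 5% (read as two-sided), intracluster correlation 0.01, 30 prescriptions per GP, 10% losses. Design and Randomisation sections: 24 teams, 1:1.

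**The plan's own figure.** Per arm, (1.96 + 0.8416)² × (0.10×0.90 + 0.07×0.93) / 0.03² gives 1,353. Design effect: 1 + 29 × 0.01 = 1.29. Total: 2 × 1,353 × 1.29 / 0.90 = 3,879, against the stated 3,878. The figure is reproduced and makes no use of covariates, so changing the rule leaves it as it is.

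**How often a predictor enters.** Under randomisation a 5% test rejects 5% of the time whatever the variable's link with the outcome. In simulation, entry rates were 4.8% to 5.6%. A true predictor is dropped about 95% of the time.

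**Effect on error rates and power.** The protocol gives no covariate strengths, so a range is assumed. R² is the share of team-mean outcome variance explained by one covariate. The simulation used normally distributed team means, 12 teams per arm without pairing, 100,000 replicates, and an effect giving about 80% unadjusted power. It compared the protocol's rule (adjust only if baseline p < 0.05) with adjustment always made.

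| R² | Type I, rule | Type I, rule, baseline p 0.05–0.20 | Type I, rule, baseline p ≥ 0.50 | Type I, prespecified | Power, rule | Power, prespecified |
|---|---|---|---|---|---|---|
| 0 | 4.9% | 4.8% | 4.9% | 5.0% | 79.2% | 77.7% |
| 0.10 | 4.6% | 6.2% | 4.0% | 4.9% | 80.0% | 82.0% |
| 0.25 | 4.4% | 8.3% | 2.8% | 5.0% | 80.5% | 88.2% |
| 0.50 | 3.7% | 11.5% | 1.1% | 5.1% | 81.6% | 97.0% |

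Power loss under the rule: 82.0 − 80.0 = 2.0 points, 88.2 − 80.5 = 7.7 points, 97.0 − 81.6 = 15.4 points. For any one covariate the 0.05–0.20 window holds about 15% of randomisations (0.20 − 0.05). Within it, prespecified adjustment keeps type I error at 4.8% to 5.0% for the three non-zero R² values.

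**Analytic cross-check.** Given covariate imbalance z and correlation ρ with the outcome at the level of the contrast, the unadjusted statistic is distributed N(ρz, 1 − ρ²). For ρ = 0.3, z = 1.64 the chance of exceeding ±1.96 is 6.7%; for ρ = 0.5, z = 1.64 it is 9.5%; for ρ = 0.5, z = 1.95 it is 12.8%. At z = 0 it is 4.0% (ρ = 0.3) and 2.4% (ρ = 0.5). This is the same pattern as in the table: too high near the threshold, too low when the arms are balanced.

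**How plausible the strengths are.** With 3,878 / 24 ≈ 162 prescriptions per team, the between-team share of team-mean variance is 0.01 / (0.01 + 0.99/162) ≈ 0.62. If a covariate acts through differences between teams, R² = 0.10 means explaining 0.10 / 0.62 ≈ 16% of between-team variance, and R² = 0.25 means about 40%. The first is modest. The second is a lot for one covariate.

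**Binary outcome.** A simulation at 10% versus 7% with 24 teams of 162 gave power under the rule versus prespecified adjustment of 71.3% versus 73.8% for the weakest assumed covariate and 56.6% versus 71.4% for the strongest single one. Type I error under the rule was 3.6% to 4.6%. I use this for direction only.

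**The case against.** A reader might infer that the rule inflates the trial's false-positive rate. It does not. Overall type I error is slightly below 5%, and the figures of 6% to 12% belong only to the window just short of significance.

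A reader might also expect adjustment to shrink the standard error by the linear-model factor √(1 − ρ²), about 5% to 13% for ρ of 0.3 to 0.5. That does not carry over to a multilevel logistic model, where adjustment for a patient-level predictor can raise the standard error while moving the estimate away from zero. The gain should be stated as power.

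Other points in the plan's favour stand in part:

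- Teams are selected in pairs by rural or urban location, with stratification by socioeconomic status and, in urban areas, team size, catchment population and proportion of immigrants (Recruitment and selection). This limits team-level imbalance. It does not balance patient-level factors: patients enter through prescriptions written after randomisation by unblinded GPs, and the Randomisation section accepts that concealment cannot be guaranteed for patients.
- For the same reason a baseline difference may reflect real selection, so the test is not wholly uninformative. With 24 teams, though, it is weak, and may leave such a difference unadjusted.
- The rule is stated in advance, is limited to published predictors, and looks at baseline data rather than outcomes. That limits abuse, but the resulting model is still unknown until the arms are compared.
- A covariate with no prognostic value costs a little if forced in: 79.2% − 77.7% = 1.5 points of power. The candidates here are, by the protocol's own condition, known predictors.
- A covariate list may exist in an analysis plan that is not shown. It would not cure a selection rule that the protocol states outright. Nor would reading the two conditions as alternatives, since baseline p-values would still decide part of the model.

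**Conclusion.** The point holds. The protocol fixes a selection rule that governs the primary model and drops each true predictor about 95% of the time, assuming a 5% test and differences due to chance alone. The cost is a primary model chosen from the trial data and a loss of power of about 2 points at R² 0.10 and 8 points at R² 0.25; larger losses need covariate strengths that may be unrealistic for a single variable. The error rate is distorted conditionally, in both directions, and not inflated overall. The sizes rest on assumed covariate strengths and on simulation without pairing; the direction holds for any covariate that is truly prognostic. The planned analysis without covariates does not repair the rule, because no analysis shows the result with a prespecified set. The fixed baseline adjustment in the economic models is sound but does not reach the effectiveness models.

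**What to change.** In the Statistical analysis section, delete the condition "and which show statistically significant differences between intervention and control group at baseline". In its place, name a fixed set of predictors taken from references 9 and 18, add the team pairing and stratification factors, and state that the set enters every model whatever the baseline comparison shows. Fix the list before any data by arm are examined.

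Under Effectiveness, extend to the CVR and clinical-parameter models the baseline-value adjustment already planned for CVR and costs in the economic evaluation. Keep the baseline table as description only, with no role in choosing covariates, and keep the unadjusted models as the sensitivity analysis.

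The cost is a sentence or two and a short list. The patient, GP and team variables are already to be collected (Sociodemographic variables and diagnostics), data for the 12 months before the index prescription are already planned (Data collection), and the sample size stays as it is.
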